# Improvdent: Improving dentures for patient benefit. A crossover randomised clinical trial comparing impression materials for complete dentures

**DOI:** 10.1186/1472-6831-12-37

**Published:** 2012-08-31

**Keywords:** Complete dentures, Edentulous, Impression material, Cost-effectiveness, Crossover trial

## Abstract

**Background:**

According to the UK Adult Dental Health Survey (2009) 15% of adults aged 65–74, 30% aged 75–84 and 47% aged >85 years are edentulous and require complete dentures. Patients’ quality of life and nutrition status are affected by poor dentures. The quality of the dental impression is the most important issue for improving the fit and comfort of new dentures. There is paucity of RCT evidence for which impression material is best for complete dentures construction. This study aims to compare two impression materials for effectiveness and cost effectiveness.

**Methods/Design:**

IMPROVDENT is a double-blind crossover trial comparing the use of alginate and silicone, two commonly used denture impression materials, in terms of patient preference and cost-effectiveness. Eighty five edentulous patients will be recruited and provided with two sets of dentures, similar in all aspects except for the impression material used (alginate or silicone). Patients will try both sets of dentures for a two-week period, unadjusted, to become accustomed to the feel of the new dentures (habituation period). Patients will then wear each set of dentures for a period of 8 weeks (in random order) during which time the dentures will be adjusted for optimum comfort. Finally, patients will be given both sets of dentures for a further two weeks to wear whichever denture they prefer (confirmation period).

Patients will be asked about quality of life and to rate dentures on function and comfort at the end of each trial period and asked which set they prefer at the end of the habituation period (unadjusted denture preference) and confirmation period (adjusted denture preference). A health economic evaluation will estimate incremental cost-effectiveness ratios of producing dentures from the two materials. A qualitative study will investigate the impact of dentures on behaviour and quality of life.

Funding: IMPROVDENT is funded by NIHR RfPB (PB-PG-0408-16300).

**Discussion:**

This trial aims to provide evidence on the costs and quality of dentures cast from two different commonly used impression materials; the intention is to significantly impact on the quality of denture production within NHS dentistry.

**Trial Registration:**

ISRCTN Register: ISRCTN01528038

UKCRN Portfolio ID: 8305

## Background

According to the UK Adult Dental Health Survey (2009) one in five adults wear dentures and 6-10% of all UK adults were edentulous rising to 15% of adults aged 65–74, 30% aged 75–84 and 47% aged >85 years
[1]. The epidemiology demonstrates an uneven distribution of edentulous patients when they are defined by age, sex, socio-economic class, and geographical area of residence. Broadly, the older the patients are in the sample the higher the number of edentulous patients, the lower the socio-economic status the higher the edentulous rate, there are more women than men who are edentulous and the prevalence in England is higher in the Midlands and North compared to the South and East. These are patients who we can expect to rely on the NHS to provide dental treatment. The dentures with which they are provided have an impact on their quality of life and nutritional status.

There are published studies which have looked at the impact of tooth loss on the Oral Health Related Quality of Life (OHRQoL) using a number of different assessment tools. Jagger et al
[2] found that ”Denture related problems had a negative impact on quality of life of both partially dentate and elderly patients”. Heydecke et al
[3] say “Wearing conventional complete dentures has a significant {negative} impact on OHRQOL”. John et al
[4] conclude “Denture status was a stronger predictor for impaired OHRQoL than demographic variables and rendered age and education almost negligible in their influence on OHRQoL”. Adam et al
[5] conclude “This study shows that after the provision of a new set of complete dentures the OHRQoL of patients improved significantly”. Ellis et al 2007
[6] state “In this study, the provision of new dentures either with a conventional technique or with a duplication technique resulted in an overall improvement in oral health-related quality of life and satisfaction”. Overall the literature shows both a significant negative impact of (old) dentures on a patients quality of life and an improvement in life quality when the patients are provided with new dentures. The literature on nutritional problems associated with the edentulous state is summarised by Ellis et al 2008
[7], who found that the literature suggested that impairment of masticatory function may lead the edentate to adapt their food choices to avoid foods that they find difficult, alter food preparation in order to cope with their masticatory inefficiencies or to swallow partially masticated food. They found that the literature further suggested that dietary limitations and inadequacies (a diet high in calories and fat, low in wholemeal bread, cereals, fruit and vegetables) may result in the edentulous having demonstrable nutritional deficiencies when compared with a similarly aged dentate population, resulting in poorer health
[7]. Provision of new dentures showed an improvement in the nutritional choices available to the patients
[7].

In an aging population the nutritional status and the quality of life of edentate individuals can be improved by the provision of good quality dentures. Experts in prosthodontics concur that the quality of the dental impression is the most important issue for improving the fit and comfort of a new denture. The choice of material for the crucial impression is important but there is paucity of evidence for which impression material is best for complete denture construction. Harwood
[8] points out that there have only been 5 randomised controlled trials (RCT) reported which looked at the choice of materials for dental impressions. Only 2 of these 5 studies looked at impressions for complete dentures (i.e. of mucosa alone). These 2 studies
[9,10] were inconclusive and they did not include the impression material used by 95% of UK dentists namely alginate
[11].

Petrie
[12] shows that among experienced USA dentists (ACP Members) the single most used impression material was polyvinyl siloxane (silicone). The Petrie
[12] and Hyde
[11] papers show a dichotomy of transatlantic opinion and practice. This proposal is for a randomised controlled trial (RCT to compare the 2 impression materials (alginate and silicone) for effectiveness and cost effectiveness, and fill the evidence gap for best practice.

## Methods

### Trial objectives

#### Primary objectives

•To establish whether there is a patient preference for unadjusted dentures produced from alginate or silicone impressions.

•To assess cost-effectiveness for dentures produced from alginate versus silicone impressions.

#### Secondary objectives

•To assess the impact of dentures produced from alginate and silicone impressions on oral health related quality of life.

•To assess comfort, mobility and chewing efficiency for dentures produced from alginate or silicone impressions.

•To assess the patients’ experience of having impressions made using alginate and silicone impression materials.

•To assess by qualitative research methodology, the impact of the dentures on patient perceived life quality.

## Design

IMPROVDENT is a single centre, randomised crossover study. This design is preferred because previous high quality studies have been successful in differentiating individual preferences for different types of prosthesis
[13-15]. For each patient the aim is to produce 2 sets of dentures which are similar apart from the impression material used to mould the fitting surface. Patients will assess the comfort, mobility and chewing efficiency of each set of dentures: the patients will be asked to state which is their preferred set of dentures.

### Recruitment

Over a 22 month period 85 edentulous patients will be recruited from the Leeds Dental Institute’s (LDI) waiting list for replacement of complete dentures and from local general dental practitioners.

Patients will be approached during standard clinic visits and will be provided with verbal and written details about the study (Patient Information Sheet and Informed Consent Document). This will include detailed information about the rationale, design and personal implications of the study.

Alternatively, patients identified by other means (such as waiting lists or review of case records) may be sent a personalised letter inviting them to take part. This letter will include a brief introduction to the study. Patients will be invited to contact the research team at the LDI to find out more information and to make an appointment to discuss the study further.

In addition to the recruitment process described above, it has been recognised that if recruitment rates from the patient waiting lists at the LDI are insufficient, then recruitment of suitable patients directly from General Dental Practice (GDP) would be beneficial. General dental practitioners will be sent an invitation letter inviting them to identify potentially suitable patients for the study. They will also receive a summary outlining the nature of the study and details of the inclusion/exclusions to identify suitable patients. General dental practitioners (GDPs) will ask suitable patients if they wish to be considered for potential inclusion into the study. Interested patients will be given a patient leaflet with a brief summary about the study and details of how to contact the research team. When a patient contacts the research team they will be invited for assessment and if suitable and willing recruited to the study using the same procedure described above for LDI patients.

Patients recruited from the LDI waiting lists will generally be referred by GDPs as more complex cases for full denture construction, e.g. patients who have worn dentures for several decades and have a seriously resorbed mandible. In contrast patients recruited directly from GDPs may not have such severe resorption and might otherwise have been treated at their own dental practice.

Following information provision, patients will have as long as they need to consider participation (at least 24 hours) and will be given the opportunity to discuss the study with their family and other healthcare professionals before they are asked whether they would be willing to take part in the study. Assenting patients will then be formally assessed for eligibility and invited to provide informed, written consent.

#### Inclusion criteria

1.Patients who are edentulous.

2.Patient is available for follow up.

3.Patient requires replacement complete dentures.

4.Patient is able and willing to complete the informed consent process.

5.Age 18 years or older at the time of signing the Informed Consent Form.

#### Exclusion criteria

1.Presence of an oral tumour.

2.Requirement for an obturator.

3.Extreme xerostomia (e.g. Sjögren’s syndrome).

4.Patients who would benefit from selective pressure impressions.

5.Known hypersensitivity to silicone or alginate.

### Randomisation and blinding

A series of randomisations and colour coding of the dentures will be introduced to ensure patients, dentists and dental nurses will be unaware of the impression material used to construct each set of dentures and the order of testing each denture made from each impression material. Dentures will be coded using a small coloured dot for identification – red or blue during the habituation period and green or yellow during the adjustment periods. It is likely that patients will form a preference for a particular set of dentures during the habituation period; dentures are re-coded after the habituation period in order that patients are unaware of which denture they are being given during the adjustment periods.

The Chief Investigator will carry out the clinical stages of denture construction up to and including the delivery of the dentures. The visits for the adjustment and assessment of the dentures will be conducted by an independent Consultant in Restorative Dentistry. The assessments of denture preference are patient reported.

Patients will undergo three randomisations (refer to Figure
1):

**Figure 1 F1:**
[figure not shown]
IMPROVDENT Trial Flow Diagram.

The initial randomisation occurs at the baseline visit using sealed envelopes to determine which tray is used to make the first impression and which impression material is used first (silicone or alginate). Envelopes are created by the trial statistician, using random block sizes, and are stored in a secure randomisation locker. The habituation randomisation occurs at the completion of denture construction to determine the colour marking (red or blue) of the dentures (silicone red/alginate blue or alginate red/silicone blue, the red denture to be tested first during habituation period). Randomisation will be via sealed envelopes created by the trial statistician. Randomisation will be blocked (random block size) to ensure balance between groups. Sealed envelopes will be stored in the secure randomisation locker.

The aim of the adjustment randomisation is to establish the order of testing during adjustment. This final randomisation will occur at the conclusion of the habituation period to determine the colour re-marking (yellow or green) of the dentures (silicone yellow/alginate green, alginate yellow/silicone green, yellow to be tested in adjustment period 1 and green to be tested in adjustment period 2). Randomisation will be blocked (random block sizes) and balanced for order of testing in the habituation period. Randomisation will be administered by telephone by CTRU, using an automated 24-hour telephone system.

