### Denture construction

The Prosthodontic Research Team at LDI has developed and published a method of producing two or more sets of dentures which are clinically similar apart from the one deliberate alteration which is to be the subject of an RCT
[16]. This methodology will be used to produce two sets of dentures which are clinically similar apart from the impression material that was used to provide the mould for the fitting surface of each denture.

The intervention at the clinical secondary impression stage is the subject of this study; the secondary impressions will be made with either alginate or silicone. To take the secondary impressions, two sets of similar, spaced (2 mm), unperforated, light-cured acrylic secondary impression trays will be constructed. A set of impression trays consist of an upper and a lower tray; each set will be numbered in the laboratory A or B. Clinically, the secondary impression trays will be trimmed to size in the mouth to remove any over extension. After trimming, the trays will be randomly allocated to either the alginate or silicone impressions. The impression trays allocated to the alginate side of the study will be ‘border moulded’ with greenstick compound in the standard way
[17] and alginate (Xantalgin®) impressions taken. The trays allocated to silicone will be ‘border moulded’ with silicone (express 3 M) and impressions taken with silicone (express 3 M). The order in which the impressions are taken will be randomised; the patients will be rested for comfort for approximately 30 minutes between taking the first set of impressions and taking the second set of impressions. If a clinically adequate impression is not achieved at the first attempt with either material the impression will be repeated, until clinical adequacy is achieved. The total time taken to make the impression and number of attempts will be recorded.

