### Statistical analysis

Preference results will be presented as a 2 × 2 table for paired data and analysed using McNemar’s test for paired data to estimate the difference in proportions of patients preferring dentures made from alginate impressions compared to those made from silicone impressions, prior to any denture adjustment. Those patients expressing a preference will be allocated to the discordant cells of the table and those expressing no preference will be allocated to the concordant cells according to whether they felt that both sets of dentures were either satisfactory or unsatisfactory. The difference in proportions will be presented with a 95% confidence interval.

OHIP–EDENT scores at the end of each adjustment period will be analysed using an ANOVA model appropriate for an AB/BA crossover design. The model will incorporate denture, period, and subject, all as fixed effects. The difference between the dentures will be estimated with 95% confidence intervals.

Differences between Likert scores (measuring comfort, mobility, chewing efficiency, comfort of impression taking, taste and preference of impression taking) for each denture will be calculated and compared using the Wilcoxon test for matched pairs.

All analyses will be conducted on the intention-to-treat (ITT) population where patients will be analysed according to the treatment they were randomised to, and the per-protocol population (if necessary), where patients will be included according to the treatment they received.

An additional analysis will test whether the differences in comfort, mobility and chewing efficiency between the two dentures varies according to the timing of the assessment (i.e. between the adjustment and confirmation periods). The 5-point Likert questionnaires are completed after adjustment period 1 (wearing the yellow denture), and also at the end of adjustment period 2 (wearing the green denture). The confirmation period requires patients to complete the 5-point Likert questionnaire side-by-side after wearing whichever denture they preferred during the 2-week period. Wilcoxon tests for matched pairs will be performed on the difference in scores between the two dentures in the adjustment and confirmation periods.

Only patients who wore and completed the assessment for both dentures in the confirmation period will be included in this analysis.

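### The adjustment randomisation is balanced for habituation order, but the OHIP-EDENT model has no term for which set was worn first in habituation, so its interval may be somewhat too wide

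*Protocol article*

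**What the plan says.** Under Randomisation and blinding (text at Figure 1), the Protocol article describes three allocations.

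- **Impressions.** A blocked envelope allocation settles the tray and the impression material used first. Denture construction repeats the second part: "The order in which the impressions are taken will be randomised".
- **Habituation.** A second allocation decides whether the silicone or the alginate set is marked red and tried first: "Randomisation will be blocked (random block size) to ensure balance between groups".
- **Adjustment.** A telephone allocation decides which set is worn in adjustment period 1. For this one: "Randomisation will be blocked (random block sizes) and balanced for order of testing in the habituation period".

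Statistical analysis then fixes the OHIP-EDENT model as an AB/BA crossover ANOVA: "The model will incorporate denture, period, and subject, all as fixed effects". Period here can only mean adjustment periods 1 and 2, because OHIP-EDENT is scored at the end of each. No term identifies the set worn first in habituation. The terms are listed outright, so this is a stated specification and not a detail left open.

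**The concern.** When an allocation is balanced on a factor, the analysis would normally carry that factor. The balance removes the factor's variation from the treatment estimate. If the factor is left out of the model, its variation is still counted in the residual, so the standard error overstates the real uncertainty.

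A fixed subject effect seems to settle this, since habituation order is a property of the patient. What acts on a within-patient comparison, however, is a property of the set: whether this particular set was the red one. It takes opposite values for a patient's two sets and bears directly on the silicone-minus-alginate difference. At stake are the width of the OHIP-EDENT confidence interval and the power of that comparison.

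**Working it through.** **Inputs.** From Sample size: 76 evaluable patients, 85 recruited, 5% significance, 80% power, all for the preference outcome. From Statistical analysis: the three model terms. The document gives neither an SD for OHIP-EDENT nor any order effect, so these appear below as an assumed range.

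**1. The plan's own figure.** With discordant proportion p and difference d, McNemar's n = (1.960·√p + 0.842·√(p − d²))² / d².

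- 30% v 60%: p = 0.90, d = 0.30, giving 76.09 (stated 76).
- 25% v 55%: p = 0.80, d = 0.30, giving 67.36 (stated 67).
- Dropout: 76/0.9 = 84.4, so 85 (stated 85).

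The stated sizes reproduce. They say nothing about OHIP-EDENT precision; 76 is carried forward only as the number of patients.

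**2. Does the subject effect absorb the order?** Take 76 fixed subject effects plus denture and period.

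- Adding a patient-level order factor gives 79 columns of rank 78, so it is absorbed.
- Adding set-level terms for first in habituation and first impression gives 80 columns of rank 80, so both are estimable and neither is absorbed.

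**3. Effect on the interval.** Write each patient's silicone-minus-alginate difference as

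d_i = δ + π·s_i + g·h_i + e_i,

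where δ is the denture effect, s_i = ±1 is adjustment order, h_i = ±1 is habituation order (+1 if silicone was red), and e_i has SD σ. Because h is balanced overall and within s, it drops out of the estimate of δ, whose true SE is σ/√76 = 0.115σ. The planned model omits h, so it estimates the residual variance as about σ² + g². The ratio of interval widths, without the term to with it, is therefore about √(1 + g²/σ²).

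| g/σ (assumed) | Width ratio | Model SE without the term, √((1 + g²/σ²)/76) |
|---|---|---|
| 0 | 1.00 | 0.115σ |
| 0.25 | √1.0625 = 1.03 | 0.118σ |
| 0.5 | √1.25 = 1.12 | 0.128σ |

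If impression order acts as well, with effect k, the ratio is √(1 + (g² + k²)/σ²): 1.01 when both are 0.1σ, 1.06 at 0.25σ each and 1.23 at 0.5σ each.

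**4. Simulation.** Two separate sets of 6,000 trials per setting with n = 76 agree with the formula. One of them used random blocks of 2, 4 or 6 (assumed sizes), with adjustment order balanced within habituation order. There the denture estimate was unbiased, and its true SE stayed near 0.114σ whatever the order effect. Across the two sets, coverage of the nominal 95% interval under the planned model was 95.5% and 95.7% at g = 0.25σ, and 97.5% and 96.6% at g = 0.5σ. With the order terms added it was between 94.7% and 95.3%.

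**The case against.** The case for leaving the model alone is strong on size.

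- **The loss is conditional.** With no order effect the width ratio is 1.00. A reader might infer that the interval is certainly too wide, but the document gives no order effect on OHIP-EDENT.
- **The larger assumed effects are extreme.** With 76 patients, a denture effect of about 0.326σ would have roughly 80% power. An order effect of 0.25σ is 0.25/0.326 = 77% of that, and 0.5σ is 153%. The 80% benchmark is itself an assumption, since the trial is powered on preference only.
- **The schedule works against a large effect.** In the Habituation period section, the sets alternate daily, are then worn for three days each, then alternate again, with free choice at the end. Being first means being first by one day. The dentures are then re-coded, and each is worn for 8 weeks with adjustment before OHIP-EDENT is scored.
- **The protocol does not predict such an effect.** It says "It is likely that patients will form a preference for a particular set of dentures during the habituation period", which might be taken as forecasting an order effect. That sentence is about preferring a particular set, not about order. The second-period preference cited from an earlier crossover study concerns the main study periods, and the planned period term covers that.
- **The cost-effectiveness ratio is not reached.** OHIP-EDENT is its effect measure, so a reader might infer that the co-primary outcome inherits the wider interval. Under Economic evaluation, Analysis, the ratio comes from differences in means with a non-parametric bootstrap, not from the ANOVA interval.
- **Impression order is not a balancing factor for the adjustment allocation.** If every randomised attribute of a set needed a term, the tray would need one too.

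All of this stands. It limits the size and reach of the point. It does not remove the mismatch between an allocation balanced on habituation order and a model that omits it, or the fact that subject effects do not cover it.

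**Conclusion.** The point holds as a modest, conditional loss of precision in a secondary outcome. If habituation order shifts the silicone-alginate difference by ±0.25 SD of the within-patient difference, the planned interval is about 3% too wide; at ±0.5 SD it is about 12% too wide; at zero nothing is lost. These figures assume 76 analysed patients and the balance that the allocations are designed to give.

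The planned analysis is valid: the estimate is unbiased and the error is on the conservative side. The document does not support any reading that the test is wrong, that false positives rise, or that the co-primary economic result is affected. Only the habituation-order term follows directly from the design; a term for impression order is optional.

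**What to change.** Add one within-patient term to the OHIP-EDENT model: set worn first (red) in habituation, yes or no for each set. Equivalently, regress each patient's silicone-minus-alginate difference on codes of +1/2 and −1/2 for adjustment order and habituation order, and report the intercept as the denture effect. The codes must be symmetric about zero for the intercept to keep that meaning. Impression order, which is also randomised and blocked, may be added in the same way.

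The cost is one sentence of analysis wording. The trial's own randomisations already determine both orders. With 76 patients the planned model leaves 76 − 2 = 74 residual degrees of freedom; the habituation term leaves 73, and both terms leave 72. State the choice before the data are examined, so that it is not a post hoc choice of model.
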